### Baseline and Clinical characteristics

Unintended weight loss before surgery is defined as [(current weight) - (weight 1 month ago)] > 5% or [(current weight) - (weight 6 months ago)] > 10%. Clinical characteristics (including risk score, length of stay at the ICU and hospital, time of mechanical ventilation, organ failure, infections, and bleeding) are extracted from medical case notes and an electronic database. This database includes the risk score based on EuroSCORE [10]. Organ failure after intervention will be aggregated from the presence of cardiac damage defined as CK-MB isoenzyme ≥ 100 μg/L and/or acute renal failure defined as postoperative serum creatinine ≥ 200 μmol/L or as need for dialysis, and/or neurologic failure defined as cerebrovascular accident or peripheral neuropathy. Bleeding is defined as abdominal bleeding or need for reoperation because of bleeding, and infection is defined as respiratory tract infection, urinary tract infection, mediastinitis, sternal wound infection, leg wound infection, and other infections (such as phlebitis and rare cases of intra-abdominal and dermatologic conditions). Mortality is defined as mortality during the period from hospital admission until the postoperative visit at the outpatient clinic.

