## Background

Malnutrition is very common in patients undergoing cardiac surgery as well as other types of surgery. For example, in a population of cardiac and abdominal surgical patients, respectively 10-25% [1,2] and 44% [3] was malnourished. Malnutrition is an independent risk factor resulting in more complications, and increased mortality rates, length of hospital stay and costs [1-3]. The lack of optimal nutrition can change myocardial substrate utilization which can have adverse effects on myocardial metabolism such as adenosine triphosphate (ATP) production and utilization [4]. For that reason, malnutrition might be an underlying risk factor for the perioperative cardiac complications observed in patients undergoing non-cardiac surgery [5]. In addition to cardiac complications, the lack of optimal nutrition can induce nutrient deficiencies which in turn can lead to the impairment of the immune system [6]. It is still common practice that patients receive only clear fluids during the period prior to surgery and the day after surgery leading to starvation of the patient over a longer period of time. As this occurs, glycogen reserves that last only a few hours will deplete with the result that further fasting induces gluconeogenesis. As this gluconeogenesis mainly depends on catabolism of body proteins it furthers the negative effects of malnutrition. We hypothesize that avoidance of malnutrition and starvation can improve cardiac metabolism and function, and might prevent protein catabolism, which would be beneficial for both cardiac and non-cardiac surgical patients.

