### Outcome measures

The main study outcomes are amino acid profile and cardiomyocytes structure at the time of cardiac surgery. Amino acid profile will be studied in blood plasma and cardiac tissue and includes determining the concentrations of all amino acids, ADMA and symmetric dimethylarginine (SDMA, ADMA's isomer that lacks direct NOS inhibitory activity). In addition, the arginine/ADMA ratio (an indicator of potential NO production) will be calculated. In cardiac tissue, also the activity of dimethylarginine dimethylaminohydrolase (DDAH, an enzyme which degrades ADMA) and arginase (an enzyme which metabolizes arginine) are measured. Cardiomyocytes structure will be assessed by histological analysis, immuno-histochemistry, and by electron microscopy.

The secondary study outcomes are cardiac perfusion, left ventricular function and cardiac glucose metabolism. ECG-gated MPS will be used for the measurement of cardiac perfusion and left ventricular function. Cardiac glucose metabolism will be measured with ^18^F-FDG PET.

BIS measured FFM will be used as parameter of nutritional status. A high FFM is related to better nutritional status and improved post-surgical outcome [9]. Other outcome parameters are cardiac muscle damage and signs of failure as measured by blood plasma biomarkers (Troponin T, CK-MB, and NT-proBNP). Blood plasma will be stored for future study of metabolic switch biomarkers. Baseline characteristics (including European System for Cardiac Operation Risk Evaluation score (EuroSCORE) [10], and unintended weight loss) will be recorded, as well as clinical parameters (intensive care unit (ICU) stay, length of hospital stay, time of mechanical ventilation, organ failure, infections, bleeding, and postoperative mortality). Finally, the concentration of ADMA will be measured in a sample of the aortic wall to investigate the relation between tissue ADMA concentrations in the aorta, and both intracellular concentrations from peripheral blood mononuclear cells (PBMC) and plasma levels.

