### Statistical analysis

The results of the enteral and parenteral group will be compared with results of the control group. Differences between the (par)enteral and control group will be analyzed with Chi-square tests for categorical variables, with unpaired t-tests for continuous variables, and with the Mann-Whitney U test for non-normally distributed data. Correlations will be analyzed with Pearson's correlation or with the Spearman rank correlation coefficient. Multiple linear and multiple logistic regression models will be used to determine if differences between groups can be explained by the effect of (par)enteral nutrition, by confounders or by both. A p-value of ≤ 0.05 will be considered statistically significant.

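### The definition of unintended weight loss subtracts in the wrong order and names no reference weight, so each criterion, read literally, is met only by weight gain

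*Protocol article*

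**What the plan says.** The protocol article gives an operational definition under Baseline and Clinical characteristics: "Unintended weight loss before surgery is defined as [(current weight) - (weight 1 month ago)] > 5" per cent. The second criterion, for the longer window, reads "or [(current weight) - (weight 6 months ago)] > 10" per cent. The two criteria are joined by *or*. Neither has an absolute value, a division or a stated base for the percentage, and no other section redefines the variable.

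Under Outcome measures the variable stands in the parenthetical list of baseline characteristics, next to the EuroSCORE: "and unintended weight loss) will be recorded, as well as clinical parameters". It is not listed there as a main, secondary or other outcome.

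The Statistical analysis section allows for covariates in general terms: "Multiple linear and multiple logistic regression models will be used to determine if differences between groups can be explained by the effect of (par)enteral nutrition". Confounding is given there as the alternative explanation, alone or alongside nutrition, but the section does not say which variables count as confounders.

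**The concern.** The quantity is called a loss, but the bracket is the change from earlier to current weight, which is negative for a loss. A negative number cannot exceed a positive threshold, so the rule as printed picks out gains. The same reversal occurs in both criteria.

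There is also a units problem. Each bracket is a number of kilograms, and it is compared with a percentage without saying of what. Reversing the subtraction alone would still leave the variable undefined close to the cut-off.

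The stake is a baseline descriptor. Programmed as printed, it would show gainers as losers and leave most true losers unmarked in the baseline table. It is the only item on recent weight history among the baseline characteristics that the article names, in a trial whose rationale is malnutrition. If it were also picked as a confounder, the inverted indicator would enter a regression.

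**Working it through.** **Inputs.** The two thresholds (5% over 1 month, 10% over 6 months), the order of subtraction and the joining *or* all come from Baseline and Clinical characteristics. The example weights are mine. The article gives no figure to reproduce on this point.

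**Notation.** C = current weight, W1 = weight 1 month ago, W6 = weight 6 months ago. The article names no denominator, so I tried both earlier weight and current weight.

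- Rule as printed, with a denominator D supplied: (C - W1)/D > 0.05 or (C - W6)/D > 0.10.
- Rule with the subtraction reversed: (W1 - C)/D > 0.05 or (W6 - C)/D > 0.10.

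**Step 1: sign.** D is positive. If C < W1 and C < W6, both left-hand sides of the printed rule are negative, so neither can exceed its threshold. This does not depend on D.

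| One-month change | C - W1 | As % of earlier weight | As % of current weight | Printed 1-month criterion |
|---|---|---|---|---|
| 80 to 74 kg | -6 kg | -6/80 = -7.5% | -6/74 = -8.1% | not met |
| 74 to 80 kg | +6 kg | 6/74 = +8.1% | 6/80 = +7.5% | met |

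The 6-month criterion behaves in the same way: 80 to 68 kg gives -12 kg, and -12/80 = -15%, so it is not met.

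**Step 2: check over a grid.** I took whole-kilogram current weights from 40 to 120 kg and every pair of higher earlier weights up to 140 kg. The number of combinations is the sum of k² for k = 20 to 100, which is 338,350 - 2,470 = 335,880. With earlier weight as denominator, the printed rule flags 0 of them and the reversed rule flags 333,054. These counts reflect the grid chosen and estimate no prevalence.

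**Step 3: the limit of the statement.** Because of the *or*, a patient with opposite changes in the two windows can be flagged. Take 80 kg six months ago, 98 kg one month ago and 92 kg now:

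- 1 month: (92 - 98)/98 = -6.1%, printed criterion not met.
- 6 months: (92 - 80)/80 = +15%, printed criterion met.

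This patient lost 6.1% in a month and is flagged, but only through the window in which weight rose. The exact statement is therefore that each printed criterion is met only by a gain over its own window, and that a patient whose weight fell over both windows is never flagged.

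**Step 4: the missing base.** For 80 to 76.1 kg in one month the loss is 3.9 kg. On earlier weight, 3.9/80 = 4.88%, which is below 5%. On current weight, 3.9/76.1 = 5.12%, which is above it. The same patient changes class with the choice of denominator.

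**The case against.** The best defence is that the name of the variable makes the intent plain. Most analysts would read the bracket as shorthand for the size of a percentage loss and would code it correctly, and nothing in the article shows that it was coded literally. That stands, and it means recomputation should depend on what the code does. It does not make the printed definition right: the article chose to give an operational rule, and the rule contradicts its own label.

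The second defence concerns weight in the trial. Table 1 does not use unintended weight loss for eligibility. The block randomization under Participants mentions no such stratum. The stated parameter of nutritional status is fat free mass by bioelectrical impedance spectrometry, which also carries the third aim, and body weight and height are measured separately at baseline. All of this stands, and it limits the severity.

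A reader might infer more in two places. One is that an inverted malnutrition indicator will distort the adjusted analyses. The article does not support that, because it names no confounders. Harm there needs two further steps: that the variable is selected, and that it is coded as printed. The other is a count of affected patients, obtained by applying the Background statement that "in a population of cardiac and abdominal surgical patients, respectively 10-25% [1,2] and 44% [3] was malnourished" to the 48 patients. That does not follow. Those are malnutrition rates from cited studies, and the article links them neither to this weight-loss rule nor to elective off-pump patients with stable angina. No number of misclassified patients can be derived from the document.

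**Conclusion.** The definition is wrong as written, in both the order of subtraction and the missing reference weight. The sign result holds for either denominator and needs no outside source.

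The severity is minor. The certain reach is one baseline variable, and only if it is coded literally; a regression is reached only if that variable is then chosen as a confounder. No main or secondary outcome is affected.

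It would be too strong to say that the rule misses every patient who lost weight, or that its sensitivity is zero: the patient with opposite changes in the two windows is a counterexample. Taking earlier weight as the base is a conventional assumption, not something the article states.

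**What to change.** Replace the two brackets by:

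- (weight 1 month ago - current weight) / weight 1 month ago x 100 > 5%, or
- (weight 6 months ago - current weight) / weight 6 months ago x 100 > 10%.

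The thresholds are the article's own and stay unchanged. The sponsor should confirm that earlier weight is the intended denominator. Then check how the variable has been derived in the database, and recompute it only if the printed formula was followed literally. The cost is one line of text, one check of the code and, at most, one derived variable run again.

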### Nutrition and administering devices

#### Enteral nutrition

During the four days before hospital admission, the enteral group will take 125 ml per day of a nutrient drink (Nutridrink Compact, Nutricia, Zoetermeer, The Netherlands) consisting of proteins, carbohydrates, fats, vitamins and minerals (Table 3). When admitted to the hospital, patients in the enteral group will receive a solution containing amino acids (PeptoPro, DSM, Delft, The Netherlands), carbohydrates (Fantomalt, Nutricia, Zoetermeer, The Netherlands), and vitamins and minerals (Phlexy-Vits, SHS International Ltd., Liverpool, United Kingdom) which will be prepared at the hospital each day. An amount of 1050 ml of the enteral nutrition will be given during 24 hours. This nutrition will be given two days before, during and two days after CABG by a computerized guidance system-placed nasoduodenal tube (Cortrak^®^, Viasys Healthcare, Wheeling, IL, USA). At the morning of surgery the position of the duodenal tube is verified. Patients are permitted to eat and drink in addition to their supplemental nutrition.

**Table 3 T3:** Composition of enteral and parenteral nutrition

	Enteral group		Parenteral group
	Drink (at home) per day	Nutrition (at hospital) per day	Nutrition (at hospital) per day
Volume (ml)	125	1050	1250
Amino acids (g)	12	80.5	40
Carbohydrates (g)	37.1	95	80
Fat (g)	11.6	1.5	50
Energy (kcal)	300	745	955
Vitamins and minerals	Yes	Yes	Yes

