#### Parenteral nutrition

Patients in the parenteral group will receive 1250 ml of nutrition (Nutriflex Lipid peri, B.Braun, Oss, The Netherlands) containing amino acids, lipids and glucose. An amount of 1250 ml of the amino acid infusion (840 mOsm/L) will be given in 24 hours for 5 days (Table 3). In addition, vitamins (Cernevit, Baxter, Utrecht, The Netherlands) and trace elements (Nutritrace, B.Braun, Oss, The Netherlands) will be added to the parenteral nutrition. This nutrition will be given two days before, during and two days after CABG. Patients are permitted to eat and drink in addition to their supplemental nutrition.

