#### Controls

The control group follows the standard protocol of the department of cardio-thoracic surgery of the AMC allowing patients to eat and drink until six hours before surgery. The day after surgery, this standard protocol prescribes a (clear) liquid diet. On the second day after surgery patients are recommended a normal diet.

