### Anesthetic and (post-)surgical procedures

Anaesthesia is induced with sufentanil 3 μg kg^-1 ^(Suftena^®^, Janssen-Cilag, Tilburg, The Netherlands) and propofolol 50-100 mg (Fresenius Kabi, Den Bosch, The Netherlands). Pancuronium bromide 0.1 mg kg^-1 ^(Pavulon^®^, Organon, Oss, The Netherlands) is given for muscle relaxation. Morphine 20 mg is given as a slow bolus injection before start of surgery. Anaesthesia is maintained with a continuous infusion of propofolol 2-5 mg kg^-1 ^h^-1^.

The off-pump technique is used for all patients. After a median full sternotomy, a few superficial and deep pericardial sutures are placed to facilitate cardiac displacement. During anastomosis, a suction-type mechanical stabilizer (Octopus 4.3, Medtronic, Minneapolis, MN, USA) is used to immobilize the target site of coronary artery. Distal myocardial perfusion is maintained using intracoronary shunt tube (Anastaflo, Edwards Lifescience, Irvine, CA, USA). The basic strategy for myocardial revascularization is in situ grafting of the internal thoracic artery to the left coronary system with complementary saphenous vein. Vein-to-aorta proximal anastomosis is performed using partial clamping or an anastomotic device.

After surgery, patients are admitted to the ICU and treated according to a standardized clinical protocol. Fluid administration consists of NaCl 0.9% and hydroxyethyl starch 6% of molecular weight 200 kDa (Haes-Steril, Fresenius Kabi, Den Bosch, The Netherlands).

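### Phlebitis counts as an infection without being limited to infective cases, while only the parenteral arm has a five-day nutrient infusion, so non-infective infusion-site events could blur the infection comparison

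*Protocol article*

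**What the plan says.** The protocol article, under Baseline and Clinical characteristics, defines infection as respiratory tract, urinary tract, mediastinal, sternal wound or leg wound infection, plus "other infections (such as phlebitis and rare cases of intra-abdominal and dermatologic conditions". It sets no criterion for when a phlebitis is infective and describes no separate count. These data come from case notes and an electronic database.

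The arms differ in how nutrition reaches the patient:

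- Parenteral nutrition: "An amount of 1250 ml of the amino acid infusion (840 mOsm/L) will be given in 24 hours for 5 days". The timing is two days before, during and two days after surgery. Peripheral or central access is not stated.
- Enteral nutrition: given in hospital "by a computerized guidance system-placed nasoduodenal tube".
- Controls: the standard departmental protocol, "allowing patients to eat and drink until six hours before surgery", with no nutrient infusion.

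Under Anesthetic and (post-)surgical procedures, intravenous fluids are described for patients in general: "Fluid administration consists of NaCl 0.9% and hydroxyethyl starch 6% of molecular weight 200 kDa". Outcome measures lists infections among the clinical parameters to be recorded, not among the main or secondary outcomes. Statistical analysis compares the fed arms with control, using chi-square tests for categorical variables and a threshold of p ≤ 0.05.

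**The concern.** Phlebitis at an infusion site can be a local reaction to the infusion, without infection. Under the definition as written, a bare phlebitis entry in the notes counts as an infection whatever its cause. The exposure most specific to one arm is the five-day nutrient infusion, so such entries could accumulate mainly in the parenteral group.

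Two questions would then share one count: whether feeding changes postoperative infection, and whether this delivery route irritates veins. An excess of local reactions could imitate a higher infection rate under parenteral feeding or hide a lower one. A harm specific to the route would also be harder to see inside a general total. Infection bears on the trial's rationale: the Background links poor nutrition to impaired immunity, and Previous studies cites fewer postoperative infections with enteral nutrition.

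**Working it through.** The article states no infection rate, phlebitis rate or power figure, so there is no figure of its own to reproduce. The calculation shows how far the definition could move the result under stated assumptions.

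**Inputs from the article.** 16 patients per arm (3 × 16 = 48); chi-square test; p ≤ 0.05; 2 + 1 + 2 = 5 infusion days. Table 2 marks nutrition from day -3 to day 2, which is six calendar days. That should be reconciled with the five days in the text, but nothing below depends on it.

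**Assumptions.** True infection risk p is equal in all arms. Added non-infective phlebitis occurs at rate f in the parenteral arm only, independently of infection. Setting f to zero elsewhere makes the contrast as large as possible for a given f.

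**Formula.** Recorded risk in the parenteral arm = p + (1 − p)f. With p = 10%:

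| f | Recorded risk | Extra events in 16 |
|---|---|---|
| 0% | 10.0% | 0 |
| 5% | 0.10 + 0.90 × 0.05 = 14.5% | 16 × 0.045 = 0.7 |
| 10% | 0.10 + 0.90 × 0.10 = 19.0% | 16 × 0.090 = 1.4 |
| 20% | 0.10 + 0.90 × 0.20 = 28.0% | 16 × 0.180 = 2.9 |
| 30% | 0.10 + 0.90 × 0.30 = 37.0% | 16 × 0.270 = 4.3 |

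The spurious difference is (1 − p)f. For p from 5% to 20% and f from 5% to 30%, it runs from 0.80 × 0.05 = 4 to 0.95 × 0.30 = 28.5 percentage points.

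**Chance of a significantly higher recorded rate in the fed group.** This sums the binomial probabilities of every table that gives p ≤ 0.05 with the fed group higher, at p = 10%. The article does not say whether a continuity correction applies, so both versions are shown. Pooling means the two fed arms combined, 32 against 16.

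| f | Parenteral v control, uncorrected | Parenteral v control, corrected | Pooled, uncorrected | Pooled, corrected |
|---|---|---|---|---|
| 0% | 1.4% | 0.1% | 0.7% | 0.1% |
| 10% | 9.5% | 1.9% | 3.3% | 0.6% |
| 20% | 25.9% | 10.0% | 8.5% | 2.6% |
| 30% | 47.4% | 26.1% | 16.0% | 6.6% |

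In the pooled group the recorded risk is the mean of the two arms; at f = 10% it is (10.0 + 19.0)/2 = 14.5%, half the single-arm excess.

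**Masking.** Suppose parenteral feeding truly halved infection from 20% to 10%. The recorded rate returns to 20% when 0.10 + 0.90f = 0.20, so f = 0.10/0.90 = 11%.

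**The case against.** The strongest reply is that phlebitis appears as an example within a list of infections, so infective phlebitis may be all that is meant. If so, an excess under parenteral feeding is a genuine complication of a randomized treatment and belongs in the comparison. This stands as a possible reading, but the text does not settle it, and extraction from routine notes makes an unqualified count likely enough to deserve a line of definition.

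A reader might infer that the outcome is loaded against parenteral feeding. The article does not support that. It gives no phlebitis rate and no access route, so neither the existence nor the size of an excess can be derived. Nor is it right that the other arms have no venous exposure: anaesthesia and postoperative fluids are intravenous for patients in general. What differs is the nutrient solution, its duration and its preoperative start.

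A reader might also infer that the definition is what prevents the trial from showing an effect on infection. Sample size is the larger obstacle. With no phlebitis at all, a true halving from 20% to 10% would reach significance in the right direction only about 11% of the time at 16 against 16 (2.4% with continuity correction).

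Pooling the fed arms is only one reading of Statistical analysis, and it weakens the effect. Finally, simply dropping phlebitis would discard genuine line infections and tilt the outcome the other way. That objection is sound and shapes the fix.

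**Conclusion.** The point holds as a minor defect in a stated definition. Phlebitis is counted without restriction to infective cases, and the five-day nutrient infusion is confined to one arm, so non-infective events could inflate recorded infection mainly there. The direction follows from the design; the size does not. Every rate in the calculation is assumed, and the distortion vanishes if there is no excess of non-infective phlebitis or if only infective cases are in fact counted. At an assumed 10% true infection and 10% added phlebitis, it amounts to 9 percentage points, or between one and two events among 16 patients.

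Amino acid profile, cardiomyocyte structure, perfusion, ventricular function and glucose metabolism are untouched. What is at risk is the reading of one recorded clinical parameter in a 48-patient proof-of-concept study.

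**What to change.** In Baseline and Clinical characteristics:

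1. State that only infective phlebitis counts as an infection.
2. Report all phlebitis, infusion-site or catheter, as a separate line for each of the three arms, so that a harm of the route stays visible.
3. Give the infection comparison with control both with and without phlebitis.

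The criterion for infective phlebitis should be fixed before outcomes are compared by arm.

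The cost is one line of definition, one more reported outcome, and a judgement from case notes on whether each phlebitis was infective. Routine notes may not always allow that judgement, which is why the comparison should be shown both ways. No treatment, visit or sample changes.

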### Setting

Figure 1 depicts a flow chart of the study protocol. The study is currently performed at the department of cardio-thoracic surgery of the AMC. Patients are informed about the study by a cardiologist and nutritionist who hand over the information letter as well as the informed consent form. A patient is included in the study when the informed consent form is signed. Subsequently, the patient can be randomized to one of the three groups: the "enteral group" (n = 16), the "parenteral group" (n = 16), or the control group (n = 16). During visits at the hospital outpatient clinic (approximately two weeks before surgery), patients are subjected to baseline measurements including blood sampling, measurement of body weight and height, bioelectrical impedance spectrometry (BIS), ECG-gated myocardial perfusion scintigraphy (MPS) and a ^18^F-fluorodeoxy-glucose positron emission tomography (^18^F-FDG PET) scan (Table 2). As part of the preoperative evaluation, patients will also undergo preoperative assessments by a cardiothoracic surgeon and an anesthesiologist.

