**Figure 1 F1:**
[figure not shown]
**Flow chart of study protocol**. BIS, bioelectrical impedance spectrometry; CABG, coronary artery bypass grafting; ^18^F-FDG PET, ^18^F-fluorodeoxy-glucose positron emission tomography; MPS, myocardial perfusion scintigraphy.

**Table 2 T2:** Study schedule

Days	Before								CABG			After			
	**-14**	**-7**	**-6**	**-5**	**-4**	**-3**	**-2**	**-1**	**0 ** **before**	**0 ** **start**	**0 ** **end**	**1**	**2**	**3**	**>21**

Informed consent	E,P,C														
Randomization	E,P,C														
Blood sampling	E,P,C								E,P,C	E,P,C	E,P,C	E,P,C		E,P,C	E,P,C
MPS	E,P,C														E,P,C
^18^F-FDG PET	E,P,C														E,P,C
BIS	E,P,C														E,P,C
Cardiac tissue										E,P,C	E,P,C				
Aortic tissue											E,P,C				
Nutrient drink		E	E	E	E										
Hospital admission						E,P		C							
Nutrition						E,P	E,P	E,P	E,P	E,P	E,P	E,P	E,P		

BIS, bioelectrical impedance spectrometry; C, control group; CABG, coronary artery bypass grafting; E, enteral group; ^18^F-FDG PET, ^18^F-fluorodeoxy-glucose positron emission tomography; MPS, myocardial perfusion scintigraphy; P, parenteral group.

Patients allocated to the enteral and parenteral group will be admitted at the hospital three days before surgery (Table 2). Patients allocated to the control group will be admitted one day before surgery.

Approximately three weeks after surgery patients will visit the outpatient clinic for measurements including blood sampling, measurement of body weight, BIS, MPS and ^18^F-FDG PET. In addition, as part of the routine clinical postoperative care patients will be seen by a cardiothoracic surgeon.

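### Admission is two days earlier in both nutrition arms, yet mortality is counted from admission and length of hospital stay has no stated start; both need a time zero common to all arms

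*Protocol article*

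**What the plan says.** **Admission.** The text below Table 2 sets a different admission day by arm: "Patients allocated to the enteral and parenteral group will be admitted at the hospital three days before surgery", whereas "Patients allocated to the control group will be admitted one day before surgery". Table 2 agrees: the enteral and parenteral arms are admitted on day -3 and control on day -1.

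**Mortality.** Baseline and Clinical characteristics fixes the window: "Mortality is defined as mortality during the period from hospital admission until the postoperative visit at the outpatient clinic". Outcome measures lists the same item among the clinical parameters: "time of mechanical ventilation, organ failure, infections, bleeding, and postoperative mortality". The closing visit is described as follows: "Approximately three weeks after surgery patients will visit the outpatient clinic for measurements". Table 2 labels that column >21.

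**Length of hospital stay.** Outcome measures names it. Baseline and Clinical characteristics gives its source, "length of stay at the ICU and hospital, time of mechanical ventilation, organ failure, infections, and bleeding) are extracted from medical case notes", together with an electronic database. Neither section says when the count starts or ends.

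**Analysis.** The Statistical analysis section compares the nutrition groups with control by unpaired t-test, Mann-Whitney U or chi-square test, at p ≤ 0.05. It does not set the clinical parameters apart as descriptive only.

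**The concern.** In this design admission marks a different moment in each arm. It is two days earlier in the 32 nutrition patients because the protocol requires it, not because of anything that happens to the patient. It is not the start of the intervention either, since Table 2 has the enteral arm taking the nutrient drink on days -7 to -4, before admission. An outcome counted from admission therefore mixes the schedule with the response to treatment.

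For mortality the anchor is written down and contradicts the name given to the outcome elsewhere. For hospital stay the anchor is left open, in a trial where the choice moves the group difference by two days. The Background links malnutrition to longer stay and higher mortality, and the section on previous studies cites shorter hospitalisation as a benefit of amino acid supplementation. Readers will therefore look at this comparison. A longer stay in the nutrition arms could be taken for slower recovery, and a real gain could be hidden. The regression models planned for confounders cannot separate the two, because the preoperative days coincide with allocation.

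**Working it through.** The article gives no power statement, effect size or SD for these outcomes, so there is no figure of its own to reproduce.

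**Inputs from the article:** admission on day -3 (nutrition) and day -1 (control); visit about three weeks after surgery; 16 patients per arm; significance at p ≤ 0.05.

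**Assumed:** two-sided testing; SD of hospital stay 2 to 6 days; preoperative daily hazard of death 0.00001 to 0.001; a visit at day 28 as an alternative to day 21.

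**1. Offset.** 3 − 1 = 2 days.

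**2. Mortality window.** Days from admission to surgery plus days from surgery to visit:

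| Visit | Nutrition arms | Control | Excess |
|---|---|---|---|
| Day 21 | 3 + 21 = 24 | 1 + 21 = 22 | 2/22 = 9.1% |
| Day 28 (assumed) | 3 + 28 = 31 | 1 + 28 = 29 | 2/29 = 6.9% |

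All the extra time is preoperative. Expected extra deaths = 32 patients × 2 days × daily hazard: 32 × 2 × 0.00001 = 0.0006, up to 32 × 2 × 0.001 = 0.064.

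**3. Length of stay, if counted from admission to discharge.** The expected difference with no treatment effect is +2 days in each nutrition arm. With a true two-day shortening of the postoperative stay it is −2 + 2 = 0.

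The chance that the offset alone reaches p ≤ 0.05 follows from the noncentral t distribution, with noncentrality 2 / [SD × √(1/n₁ + 1/n₂)] and n₁ + n₂ − 2 degrees of freedom. Example, SD 3 and 16 versus 16: the standard error is 3 × √(1/16 + 1/16) = 1.061, the noncentrality is 2/1.061 = 1.89 on 30 degrees of freedom, and the probability is 0.446.

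| Assumed SD (days) | 16 vs 16 | Nutrition arms pooled, 32 vs 16 |
|---|---|---|
| 2 | 78% | 89% |
| 3 | 45% | 57% |
| 4 | 28% | 36% |
| 5 | 20% | 25% |
| 6 | 15% | 19% |

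**4. With surgery as the start for both outcomes.** The offset in stay is 0 days, and the mortality window is about 21 days in every arm.

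**The case against.** **The article never says that stay is counted from admission.** This stands. A reader might infer that the plan builds a two-day bias into hospital stay, but only the data source is given. An article may leave start and end points of a recorded variable to the full protocol. What remains is that admission to discharge is the ordinary meaning of hospital stay taken from case notes, and that the arm-dependent admission days are stated.

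**The probabilities are conditional.** This also stands. They need that reading, an assumed SD and a t-test, whereas stay is often skewed and the plan would then use Mann-Whitney. If total bed use is the quantity of interest, the two extra days are also a genuine consequence of giving the nutrition. They mislead only when read as recovery.

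**Mortality is hardly affected.** This is correct. A reader might infer that mortality itself differs between arms by design. Only the window does, and the added days fall before elective surgery in patients with stable angina. Nor is the window undefined for patients who die: a death before the visit lies inside the period and is counted. Starting at admission does capture deaths during in-hospital study nutrition, which starting at surgery would lose. That favours randomisation as the common anchor, and does not justify one that varies by arm.

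**Complications.** It is tempting to say that infections, bleeding and organ failure share the problem and should all be counted from surgery. The article states no in-hospital window for infections, its organ failure definition already refers to the time after intervention, and several listed events can only occur postoperatively. Its infection list includes phlebitis, so a start at surgery would drop preoperative events in the nutrition arms.

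**Standing of these outcomes.** They are neither main nor secondary outcomes, and none of the three aims rests on them. This limits the severity.

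**Conclusion.** The point holds in limited form. Two things are stated: the two-day difference in admission, and a mortality window that opens at admission although the outcome is called postoperative. The window is about 24 versus 22 days. At the assumed hazards this adds fewer than 0.1 expected deaths among 32 patients, so for mortality it is a fault of definition and consistency, not a material bias.

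Length of stay carries the weight, but conditionally. If it runs from admission to discharge, the nutrition arms are two days longer with no treatment effect, and a two-day benefit would show as zero. On that reading the offset alone is significant in about 45% of trials at 16 versus 16 with SD 3 days, within 15% to 78% over SDs of 6 to 2 days. The width of that range reflects the lack of an SD in the article. Because these are recorded clinical parameters in a 48-patient proof-of-concept study, the severity is minor to moderate.

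**What to change.** - **Length of hospital stay:** define it as days from surgery (day 0) to discharge in all arms, and report preoperative days separately so that total bed use stays visible.
- **Mortality:** define it as death from any cause from an anchor common to all arms to one fixed day within the existing follow-up, for example day 21. Randomisation (day -14 in Table 2) keeps preoperative deaths. Surgery is acceptable if deaths before it are reported separately. Reconcile the wording in Outcome measures with that in Baseline and Clinical characteristics. A later cut-off, such as day 30, would need a vital-status check after the last contact that the article describes.
- **Infections:** report from randomisation, with the postoperative period shown separately.

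The admission schedule need not change. The cost is the wording of the definitions, since dates of admission, surgery and discharge are routine hospital records. For stay, the change removes the two-day offset entirely.
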